## Version 2.6

the rat. J Auton Nerv Syst. 1997 Mar 19;63(1-2):46-50.)

- The Baekhogainsam-Tang granules will be purchased from Hanpoong Pharmaceutical & Food Co., Ltd. Baekhogainsam-Tang (BIT; Baihu Jia Renshen-tang in Chinese; Byakko-ka-ninjin-to in Japanese) is known to be effective in treating symptoms such as flushing, thirst, and sweating due to dehydration during the chronic stage of high fever. BIT, widely used in Korea, China, and Japan, has been approved by the Korea FDA for clinical use in patients complaining of sore throat and thirst. Thus, BIT is expected to have a similar effect while reducing the dose of pilocarpine by treating xerostomia caused by radiotherapy or Sjogren's syndrome. In this clinical trial, the only experimental group was set to administer BIT 4 g three times a day, referring to the permitted dosage of Hanpoong Pharmaceutical & Food Co., Ltd.
- The results of representative studies on the stability of long-term treatment of BIT for xerostomia are as follows.
  - Using Sprague-Dawley (SD) Rat as an experimental animal, a single-dose toxicity test and a 13-week repeated-dose toxicity test were conducted for BIT (TJ-34). In the single-dose toxicity test, 2g/kg and 8g/kg were administered to 10 SD rat groups (5 males and 5 females). No adverse reactions related to death or medication were observed, and there were no abnormal findings in subsequent autopsy. The lethal dose is estimated to be 8 g/kg.
  - In the repeated-dose toxicity test, SD rat was divided into control group (n=40, 20/sex, 0 mg/kg) and experimental group 1 (n=20, 10/sex, 125 mg/kg), experimental group 2 (n=20, 10/sex, 500 mg/kg), and experimental group 3 (n=40, 20/sex, 2000 mg/kg), and some of the control group (n=20, 10/sex, 0 mg/kg) and experimental group 3 (n=20, 10/sex, 2000 mg/kg) were additionally observed for 4 weeks after the end of administration. No adverse reactions related to death or medication were observed during the experimental process,

## Version 2.6

and body weight and water and feed intake were not affected by medication. No change was observed in urine and ophthalmic tests after the end of administration, and no change was observed in hematologic and biochemical tests. In post-experimental autopsy, no abnormal findings related to medication were observed in organ weight, visual and histologic examination. In conclusion, the nontoxic dose of BIT is estimated to be 2000 mg/kg/day in a laboratory setting. (Minematsu S., Yoshinaga K., Takei H., et al. A single oral dose toxicity study and a 13-week repeated dose study with a 4-week recovery period of TSUMURA Byakko-ka-ninjin-to (TJ-34) in rats. Japanese Pharmacology and Therapeutics 1995 23:SUPPL. 7 (169-189))

**4.4. Necessity of the clinical trial**

- Similar to pilocarpine, BIT would effectively relieve symptoms in patients with intractable xerostomia. We hypothesized that patients with intractable xerostomia taking both BIT and low-dose pilocarpine would have similar symptom relief but fewer side effects compared with those taking only high-dose pilocarpine. Thus, we aimed to ascertain whether combined administration of BIT herbal medicine and low-dose pilocarpine can demonstrate both non-inferior efficacy and fewer side effects in patients with frequent intractable xerostomia (patients who underwent radiation therapy to the head and neck or with Sjogren's syndrome) than the administration of only high-dose pilocarpine.

**4.5. Evidence for co-administration test design**

- Pilocarpine, an acetylcholine muscarinic M3 receptor agonist, functions as a sialagogue that stimulates the secretion of exocrine gland.
- However, since the half-life of pilocarpine is short within 3 hours, and there is no cumulative effect, it should be taken several times per day (2-4 times). Meanwhile, the side effects of pilocarpine are characterized by excessive parasympathetic nerve-like effects. These include headache, visual field disorder, tears, sweating, dyspnea, gastrointestinal dystrophy, nausea,

## Version 2.6

vomiting, diarrhea, atrioventricular block, tachycardia, bradycardia, hypotension, hypertension, shock, delirium, arrhythmia, and progression. However, there are no other drugs available to patients with xerostomia in actual clinical practice due to pilocarpine' side effects.

- In this study, we want to confirm the effect of administrating both pilocarpine at half dose of commercial dose (previous clinical trial reported that half dose of pilocarpine was significantly less effective than the commercial dose) and Baekhogainsam-Tang (increasing salivary gland secretion, and improving the salivary gland secretion of pilocarpine) compared to administrating only pilocarpine at commercial dose. In other words, the design basis and goal of this study is to verify that the co-administration of Baekhogainsam-Tang has the same efficacy and reduced side effects while reducing the administration of pilocarpine.
- The paper on the basis of co-administration  
Pilocarpine, a muscarinic agonist, significantly increases salivary gland secretion, but its action is inhibited by anticholinergic drugs such as oxybutynin and propionate. In animal experiments, the salivary glands' stimulation of pilocarpine inhibited by oxybutynin was significantly recovered when BIT was co-administered.

[figure not shown]

Fig. 4. Effect of BN on salivary secretions (1–3 h) in anesthetized rats treated with oxybutynin and pilocarpine. BN was administered p.o. just before administration of oxybutynin. After 10 min, pilocarpine was injected i.p. Each column and vertical bar represents the mean  $\pm$  S.E. of six animals. \* $P$  < 0.05 and \*\* $P$  < 0.01 compared to oxybutynin (10 mg/kg, p.o.) + pilocarpine-treated group (8 mg/kg, i.p.).

( Masaru S., Kazuhiro G., Hiroyuki I.,

Version 2.6

et al. Effects of Byakko-ka-ninjin-to on salivary secretion and bladder function in rats. J  
Ethnopharmacol. 2005 Nov 14;102(2):164-9.)

## 5. The clinical trial drug information

### 5.1. Overview of clinical trial drugs

#### 5.1.1. Pilocarpine

|                               |                                                                                                                                                                                                                          |
|-------------------------------|--------------------------------------------------------------------------------------------------------------------------------------------------------------------------------------------------------------------------|
| Product name                  | Pilogen Tab.                                                                                                                                                                                                             |
| Manufacturer                  | CTC Bio, Inc.
(Seoul, Republic of Korea)                                                                                                                                                                              |
| Approval date                 | 2008-Jun-18                                                                                                                                                                                                              |
| Formulation                   | white circular film coating tablet                                                                                                                                                                                       |
| Components /
Amounts       | Pilocarpine Hydrochloride 5 mg                                                                                                                                                                                           |
| Authorized
efficacy effect | The treatment of symptoms of dry mouth from salivary gland dysfunction caused by radiotherapy for head and neck cancer.

The treatment of symptoms of dry mouth or dry eye in patients with Sjogren's syndrome.    |
| Dosage &
Administration    | Experimental group: half table (2.5 mg) four times a day, taken orally for 12 weeks

Control group: one tablet (5 mg) four times a day, taken orally for 12 weeks (four times: after each meal and before bedtime) |
| Storage                       | Airtight container, room temperature (1-30°C)                                                                                                                                                                            |

#### 5.1.2. Baekhogainsam-Tang

|               |                                                                         |
|---------------|-------------------------------------------------------------------------|
| Product name  | Baekhogainsam-tang Ext. Granule                                         |
| Manufacturer  | Hanpoong Pharmaceutical & Food Co., Ltd.
(Jeonju, Republic of Korea) |
| Approval date | 1979-Sep-18                                                             |

Version 2.6

|                            |                                                                                                                                                         |                          |          |                  |                            |
|----------------------------|---------------------------------------------------------------------------------------------------------------------------------------------------------|--------------------------|----------|------------------|----------------------------|
| Formulation                | grayish-brown granule                                                                                                                                   |                          |          |                  |                            |
| Components /
Amounts    | Single dose (4 g / dose)                                                                                                                                |                          |          |                  |                            |
|                            | Application category                                                                                                                                    | Scientific name          | standard | Amount (mg)      | Active substance capacity  |
|                            | Main component                                                                                                                                          | Anemarrhena Rhizome      | KP       | 2,000            |                            |
|                            | Main component                                                                                                                                          | Gypsum                   | KHP      | 5,330            |                            |
|                            | Main component                                                                                                                                          | Licorice                 | KP       | 660              | 13.2 mg as glycyrrhizinate |
|                            | Main component                                                                                                                                          | Oryzae Semen             | KHP      | 3,300            |                            |
|                            | Main component                                                                                                                                          | Ginseng                  | KP       | 1,000            | 2.0 mg as ginsenoside Rb1  |
|                            |                                                                                                                                                         | Soft extract             |          | 830              |                            |
|                            | Diluent                                                                                                                                                 | Lactose Hydrate          | KP       | 2,260            |                            |
|                            | Excipients                                                                                                                                              | Corn Starch              | KP       | Quantum sufficit |                            |
|                            | Excipients                                                                                                                                              | Hydroxypropyl Cellulose  | KP       | Quantum sufficit |                            |
|                            | Excipients                                                                                                                                              | Sucrose Fatty Acid Ester | KP       | Quantum sufficit |                            |
|                            | Excipients                                                                                                                                              | Magnesium Stearate       | KP       | Quantum sufficit |                            |
|                            | Excipients                                                                                                                                              | Light Anhydrous Silicate | KP       | Quantum sufficit |                            |
|                            |                                                                                                                                                         | Total                    |          | 4,000            | 100%                       |
| Authorized efficacy effect | The treatment of symptoms such as flushing, thirst, and sweating                                                                                        |                          |          |                  |                            |
| Dosage &
Administration | 
Experimental group: One packet (4 g) three times a day, taken orally for 12 weeks
(three times: before each meal)
 
Control group: None
 |                          |          |                  |                            |
| Storage                    | Airtight container, room temperature (1-30°C)                                                                                                           |                          |          |                  |                            |

## 5.2. Packing and labeling of clinical trial drugs

- Among the clinical trial drugs in this study, pilogen tabs are manufactured by CTC Bio, Inc., and Baekhogainsam-tang Ext. Granules are manufactured by Hanpoong Pharmaceutical & Food Co., Ltd., and delivered to the Clinical pharmacy of Kyung Hee University Medical Center. The drugs shall be labeled as follow in accordance with Article 69-6 of the Regulations on the Safety of Drugs, etc (Amended on Mar. 23, 2013). The clinical pharmacy of Kyung Hee University Medical Center labels drugs and delivers them to Myongji Hospital, Inha University Hospital, Kyung Hee University Hospital at Gangdong's clinical pharmacy.
- Depending on the visit schedule of the participants, clinical trial drugs are packed in airtight container for 30 days from 'Visit2' to 'Visit 4'.

1. Mark "for clinical trials"
2. Code name of the product or general name of the principal component
3. Manufacturing number and valid deadline or re-inspection date
4. Storage methods
5. Trade name and address of the person who has received approval for the clinical trial plan
6. Indication "Not available for use for purposes other than clinical trials"

## 5.3. Methods of management and storage of clinical trial drugs

- The clinical trial pharmacist is responsible for the acquisition, storage, preparation, management, and return of drugs used in clinical trials. The clinical trial pharmacist shall confirm in writing the receipts and quantity of clinical trial drugs received, sign them, and manage them appropriately.
- Clinical trial drugs are administered by the clinical trial pharmacist according to the principal investigator's prescription, and the clinical trial pharmacist must accurately record the

Version 2.6

clinical trial drugs and management given to each participant.

- This clinical trial is an open clinical trial, identified by the test subject identification number, and the clinical trial drug prescribed to each test subject and the returned clinical trial drug should be properly recorded.
- When the clinical trial is suspended or terminated, the clinical trial pharmacist must return the unused clinical trial drug to the clinical pharmacy of Kyung Hee University Medical Center and store the return certificate, and the clinical pharmacy of Kyung Hee University Medical Center must discard the returned clinical trial drug.

## **6. The duration of the study**

- IRB approval date ~ 4 years

## **7. Test subjects**

- Patients with frequent intractable xerostomia (patients who underwent radiation therapy to the head and neck or with Sjogren's syndrome)

## **8. Inclusion criteria, exclusion criteria, sample size, and basis for calculation**

### **8.1. Inclusion criteria**

- One or more of the following
  - Patients who undergone radiation therapy to the head and neck
  - Patients with Sjogren's syndrome with both followings
    - (1) positive anti-Ro/SS-A antibody reaction
    - (2) Saliva flow rate (Unstimulated)  $\leq 0.1\text{mL/min}$

## Version 2.6

- unstimulated SFR  $\leq$  0.25 ml/min
- VAS score for dry mouth over the past one month  $\geq$  4
- age  $>$ 19 years
- compliance with all written informed consent

**8.2. Exclusion criteria**

- Patients with the following past medical history
  - heart failure
  - medication-refractory hypertension (systolic blood pressure  $\geq$  160 mmHg or diastolic blood pressure  $\geq$  100 mmHg)
  - bronchial asthma
  - arrhythmia accompanied by clinical symptoms (fainting, palpitation, or shortness of breath) or requiring treatments (sinus failure, atrial conduction block, atrial fibrillation, atrial junction dependent tachycardia, ventricular tachycardia)
  - coronary artery disease
  - asthma, chronic obstructive pulmonary diseases, chronic bronchitis
  - inborn errors of amino acid metabolism
  - hepatic encephalopathy
  - ophthalmic diseases (such as narrow angle glaucoma, peripheral retinopathy, and iritis)
- Clinical laboratory test results falling within the following ranges (within 7 days prior to the start of clinical trial drug administration)
  - hemoglobin  $<$  8.0 g/dL
  - aspartate transaminase (AST) or alanine transaminase (ALT)  $>$  3 times the upper limit of each hospital standard
  - total bilirubin  $>$  2 times the upper limit of each hospital standard

## Version 2.6

- creatinine >1.5 times the upper limit of each hospital standard, or creatinine clearance  $\leq$  60 mL/min
- Patients taking following medications are also excluded: coumadin, heparin, warfarin, aspirin, anticholinergics, first-generation antihistamines, antidepressants with anticholinergic effects, monoamine oxidase inhibitors, diuretics, mineralocorticoids,  $\beta$ -adrenaline antagonist, or digitalis; patients taking low-dose aspirin or  $\beta$ -adrenaline antagonist can participate in the protocol based on the cardiologist's opinion.
- pregnancy or lactation, disagreement with proper contraception
- Failure to use appropriate contraception methods (male participants), participants who did not agree to contraception for 4 weeks after the end of administration of the trial drug (both male and female)
- galactose intolerance, Lapp lactase deficiency, or glucose-galactose malabsorption
- difficulty in oral administration of a clinical trial drug
- significant hypersensitivity to Baekhogainsam-Tang or components
- significant hypersensitivity to pilocarpine
- Participants who is deemed unsuitable for participation in clinical trials at the discretion of the investigator due to various reasons including screening test results
- cognitive disorder; inability to read and write

**8.3. Sample size**

- 120 participants (Experimental group 60, control group 60)
- Sample size by clinical trial institution

|  |                                     |                                     |                  |                                           |       |
|--|-------------------------------------|-------------------------------------|------------------|-------------------------------------------|-------|
|  | Kyung Hee University Medical Center | Inha University College of Medicine | Myongji Hospital | Kyung Hee University Hospital at Gangdong | Total |
|--|-------------------------------------|-------------------------------------|------------------|-------------------------------------------|-------|

Version 2.6

|                    |    |    |   |    |     |
|--------------------|----|----|---|----|-----|
| Experimental group | 32 | 16 | 2 | 10 | 60  |
| Control group      | 32 | 16 | 2 | 10 | 60  |
| Total              | 64 | 32 | 4 | 20 | 120 |

- Competitive recruitment
- Sample size in Kyung Hee University Medical Center: 64 (experimental 32, control 32)

#### 8.4. Basis for sample size calculation

- The aim of this prospective, randomized, open-label, parallel-group, multi-center, and controlled trial is to ascertain whether combined administration of BIT herbal medicine and low-dose pilocarpine can demonstrate both non-inferior efficacy and fewer side effects in patients with frequent intractable xerostomia (patients who underwent radiation therapy to the head and neck or with Sjogren's syndrome) than the administration of only high-dose pilocarpine.
- The assumptions for calculating the valid sample size are as follows.
  - ① One-sided Z test (Non-inferiority test)
  - ② Level of significance ( $\alpha$ ) = 0.05 (Considering this is an intervention study)
  - ③ Type 2 error ( $\beta$ ) = 0.1 (Power of the test = 90%)
  - ④ Experimental group: Control group = 1 : 1 ( $\lambda=1$ )
  - ⑤ Primary outcome: unstimulated salivary flow rate (SFR) after 12 weeks of treatment
- $\sigma = 0.35$  / d (non-inferiority limit) = 0.21

In the previous study, the mean  $\pm$  standard deviation (SD) of unstimulated SFR for 5 mg pilocarpine therapy vs placebo group after 12 weeks of medication, respectively, were  $0.38 \pm 0.48$  vs  $0.17 \pm 0.13$  mL/min ( $p < 0.001$ ). Based on these results, the SD was calculated to be 0.35.

In consideration of the exploratory aspects of the clinical trial, the point estimation ( $\mu_{CIH}$  -

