## Version 2.6

disadvantage that pilocarpine should be taken frequently and continuously due to its short action time low cumulative effect.

- In this study, the control group was set to administer the common dose of pilocarpine, and the experimental group was set to administer half dose of pilocarpine together with Baekhogainsam-Tang.

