#### **13.3.1.2. Statistical methods**

- A 95% confidence interval (95% CI) will be used to analyze primary outcomes.
- We will calculate the 95% CI of the mean difference in the unstimulated SFR between the two groups after 12 weeks of medication. If the lower end of the 95% CI of the mean difference is greater than the non-inferiority limit ( $-0.21$ ), it will be concluded that the experimental group is not inferior to the control group.
- For further analysis, if the SFR between the two groups satisfy the normality test, a t-test will be performed to compare the two groups in terms of the primary outcomes; otherwise, the Mann-Whitney U test will be performed. If there is a significant difference in baseline values between the two groups, repeated-measures analysis of covariance (ANCOVA) will be performed.

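### The planning SD of 0.35 pools in a placebo SD although neither arm receives placebo; if the cited pilocarpine SD of 0.48 holds in both arms, power at the planned one-sided 0.05 is about 69%, not 90%

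*Protocol*

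**What the plan says.** Section 8.4 of the protocol, repeated in the sample-size part of the summary, plans the primary comparison of week-12 unstimulated salivary flow rate as follows:

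- Test: "One-sided Z test (Non-inferiority test"), with significance level "0.05 (Considering this is an intervention study").
- Type II error 0.1, i.e. "Power of the test = 90" per cent.
- Allocation: "Experimental group: Control group = 1 : 1".
- Margin: "d (non-inferiority limit) = 0.21" mL/min.
- Source data: one earlier Sjögren's trial, with 12-week mean ± SD of 0.38 ± 0.48 mL/min on pilocarpine 5 mg and 0.17 ± 0.13 mL/min on placebo.
- SD: "Based on these results, the SD was calculated to be 0.35".

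The result is 48 evaluable per arm, raised to 60 per arm (120 in total) for 20% dropout.

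On the arms, section 4.3.1.1 says: "the control group was set to administer the common dose of pilocarpine, and the experimental group was set to administer half dose of pilocarpine together"; the herbal medicine is the other component. Section 9.3 confirms that both groups take pilocarpine four times a day.

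The decision rule in section 13.3.1.2 is: "If the lower end of the 95% CI of the mean difference is greater than the non-inferiority limit" (−0.21), the experimental group is declared non-inferior.

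**The concern.** The SD in a sample-size calculation should describe the patients who will be compared. Here the two groups are pilocarpine 5 mg and half-dose pilocarpine plus the herbal granules. The only quoted SD that belongs to a regimen used in this trial is 0.48. Pooling it with the much smaller placebo SD of 0.13 lowers the planning value by about a quarter, and the protocol gives no reason for doing so.

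The choice also fits poorly with the other planning inputs. The margin of 0.21 is the difference between the same two means, so the 5 mg arm's mean is carried over while its SD is diluted. The formula yields 48 only if the true difference is zero, which means that the experimental arm does as well as pilocarpine 5 mg. It is hard to see why an arm with that response would have the spread of untreated patients.

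A non-inferiority conclusion depends on the width of the confidence interval. If the SD is understated, a regimen that really is non-inferior has a larger chance of an inconclusive result than the 10% the protocol states, and such a result is easily misread as inferiority.

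**Working it through.** **Inputs.** Margin d = 0.21, σ = 0.35, one-sided α = 0.05, power 90%, 1:1 allocation, 48 evaluable per arm (all section 8.4). Source SDs are 0.48 and 0.13 (section 8.4). The true difference is not stated in words, but the printed formula gives 48 only with zero. Forty-eight is the relevant number because section 13.1.3 makes the per-protocol set the main analysis when the two sets disagree.

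**1. Reproduce the plan's sample size.**
n = 2σ²(z_α + z_β)²/d² = 2 × 0.35² × (1.645 + 1.282)²/0.21² = 47.6, rounded up to 48. With 20% dropout, 48/0.8 = 60. Both match. Power at n = 48 on these inputs is 90.2%. The arithmetic is sound.

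**2. Find where 0.35 comes from.**
Root mean square: sqrt((0.2304 + 0.0169)/2) = 0.352, which matches.
Plain mean: (0.48 + 0.13)/2 = 0.305, which does not.
So 0.35 pools a pilocarpine variance with a placebo variance.

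**3. Power at 48 per arm with other SDs.**
SE = sqrt((s_c² + s_t²)/48), and power = Φ(0.21/SE − z). Use z = 1.645 for the planned one-sided 0.05. Use z = 1.960 if the 95% CI in section 13.3.1.2 is two-sided.

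| Control SD | Experimental SD | SE | 0.21/SE | Power, one-sided 0.05 | Power, two-sided 95% CI |
|---|---|---|---|---|---|
| 0.35 | 0.35 | 0.0714 | 2.939 | 90.2% | 83.6% |
| 0.48 | 0.13 | 0.0718 | 2.926 | 90.0% | 83.3% |
| 0.48 | 0.25 | 0.0781 | 2.688 | 85.2% | 76.7% |
| 0.48 | 0.35 | 0.0857 | 2.449 | 78.9% | 68.8% |
| 0.48 | 0.48 | 0.0980 | 2.143 | 69.1% | 57.3% |

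Using the noncentral t in place of the normal changes the last row only slightly, to 68.5% and 56.4%.

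**4. Read the table.** With the control SD at 0.48, the stated 90% at one-sided 0.05 returns only in the row where the experimental arm has the placebo SD. The SD input alone accounts for the fall from 90% to 69%. The further fall to 57% comes from a different source: the decision rule, if two-sided, works at one-sided 0.025 while planning used 0.05. That mismatch on its own takes SD 0.35 from 90% to 84%.

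**5. Scale.** If all 60 per arm were analysed with no loss, SD 0.48 in both arms would give 77.4% (one-sided 0.05) or 66.9% (two-sided 95% CI). Reaching 90% at SD 0.48 would take 90 evaluable per arm at one-sided 0.05, or 110 at one-sided 0.025.

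**The case against.** The strongest objection is that 0.48 may not carry over to this trial.

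- The source is a Sjögren's trial. This trial also enrols irradiated patients, for whom no SD is quoted.
- Section 8.1 caps unstimulated flow at 0.25 mL/min for everyone and at 0.1 mL/min for Sjögren's patients. A mean of 0.38 with an SD of 0.48 for a quantity that cannot be negative implies strong right skew, so a few high responders may drive that SD. Whether such patients would be eligible here cannot be settled from the protocol.
- No SD is given for half-dose pilocarpine plus the herbal medicine. At a common SD of 0.40, for example, the same formula gives SE 0.0816 and power of about 82% (one-sided 0.05) or 73% (two-sided 95% CI).

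This stands, and it is why the result must be given as a range. It does not rescue 0.35, because the protocol does not argue for that value on any of these grounds. The caps also limit baseline flow, not the week-12 response.

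Three stronger readings are tempting but not supported:

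- A reader might infer that the SD alone brings power down to 57%. It does not. At the protocol's own planning alpha the SD gives 69%, and the lower figure also needs the two-sided reading of the interval.
- A reader might infer that the protocol contradicts itself by giving the experimental arm the placebo SD. The text assigns no SD to either arm; it uses one common σ. Equal means do not strictly require equal SDs, so the argument is one of plausibility.
- A reader might infer a calculation error. There is none after σ is fixed.

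**Conclusion.** The concern holds as a fault in a planning input. The SD of 0.35 depends on a placebo SD that belongs to neither arm, and the stated 90% power depends on it. With 48 evaluable per arm, margin 0.21, equal means and one-sided 0.05, power is about 69% if SD 0.48 applies to both arms and about 79% if the experimental SD is 0.35. In the first case a truly non-inferior regimen would fail about 31% of the time instead of 10%. If the decision uses a two-sided 95% CI, the corresponding powers are about 57% and 69%, and 84% at SD 0.35 in both arms.

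These figures assume that the cited 0.48 carries over to the control arm and, for the lower figure of each pair, to the experimental arm as well. The protocol can neither confirm nor refute that, so it cannot be said that power simply is 69% or 57%. The consequence is a greater risk of an inconclusive trial. An understated planning SD does not inflate the type I error or make a false claim of non-inferiority more likely.

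**What to change.** In section 8.4 and in the summary:

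1. Base the SD on the cited pilocarpine arm (0.48), or give a reason for another value, for instance the entry caps on flow.
2. Restate the power of the existing design with 48 evaluable per arm over SD 0.35 to 0.48, at the alpha the decision rule really uses. That is about 90% down to 69% at one-sided 0.05, or about 84% down to 57% with a two-sided 95% CI. State which of the two applies.
3. If week-12 flow data are available pooled and blind to arm, restate power from their SD. The protocol does not say whether such data exist, so this step is conditional.

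Baseline-adjusted ANCOVA, which section 13.3.1.2 now makes conditional on a significant baseline difference, may add some precision. It should not be presented as making up the shortfall. The protocol gives no baseline-to-week-12 correlation, and with baseline flow confined to 0 to 0.25 mL/min the baseline SD cannot exceed 0.125, so the gain may be small.

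The cost is a few revised sentences and power figures in two places. No patients are added and the conduct of the trial does not change.
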